### Randomized controlled trial

Eligibility for Phase II will be judged by Questionnaire A and confirmed by Questionnaire B because COVID-19 vaccination status may change during the interval between the two phases. Eligible participants will be assigned to the intervention or control arm at a 1:1 ratio chronologically, according to the sequentially numbered allocation list, which was determined by a series of random numbers generated with Microsoft Excel 2010 (Microsoft Corp., Redmond, WA, USA) prior to recruitment. College students with the order of enrollment corresponding to the smaller half of random numbers will be allocated to the intervention arm, and the rest will be allocated to the control arm. This experimental study is single-blind whereby participants will be unaware of what interventional message will be given to them. Of note, to ensure the reliability of the data, all the participants will receive a simple investigate training in word and be asked to contact their grandparents before completing the Questionnaire B.

At Phase II, a web-based health education package about COVID-19 will be provided to college students in the intervention arm for one week via the research’s WeChat Official Account (a China-based marketing platform with the functions of gathering followers and sending them targeted content). The intervention arm will receive a 5-min web-oriented multicomponent education package at Day 1, 4 and 7, whereas the control arm will not receive this package, reflecting the situation of older adults receiving COVID-19 booster dose under the influence of the current vaccine promotion policy (Table 3). The intervention package consists of two parts: COVID-19 related information and testimony from older adults who received COVID-19 booster.

Related information will be established based on knowledge, attitude, and practice (KAP) model, a framework which has been used to develop behavior change interventions in other settings, and be presented in the form of questions and answers and cover the accompanying themes: (1) current situation and relevant policies of COVID-19 vaccination among older adults in China, (2) reasons to get COVID-19 booster doses, (3) benefits and effectiveness of COVID-19 booster, (4) safety of COVID-19 vaccines, (5) indications and contraindications of vaccination, (6) precautions for vaccination [29]. These materials could be expected to specifically address these barriers against COVID-19 vaccination among older adults, including concerns about vaccine effectiveness, adverse effects, and being unsuitable for vaccination [30]. Additionally, some research found that narrative persuasion is also an effective means to promote vaccination [31, 32]. Based on the cases of older adults who successfully received COVID-19 vaccine reported by mainstream media, appropriate modifications are made to form intervention materials for narrative persuasion.

After the 7-day intervention, two weeks will be left for the participants in the intervention arm to persuade their grandparents to receive booster injections. Meantime, they will receive a daily short message service (SMS) reminder written on the basis of loss frames, which turned out to have a stronger persuasive effect than gain frames, to remind them to persuade their grandparents [32, 33]. At Day 22, participants in both arms will complete Questionnaire C to record their grandparents’ latest vaccination status and changes on their attitude and willingness towards booster doses.

To improve follow-up rates, participants will receive another symbolic reward (CNY 3, or USD 0.45) for each completed questionnaire. If they complete all follow-ups, they will receive an additional reward (CNY 8, or USD 1.2).

**Table 3 Tab3:** Schematic diagram of intervention

Content	Day 1	Day 4	Day 7	Day 8–21
Current situation and relevant policies of COVID-19 vaccination among older adults in China	√			
Reasons for receiving a COVID-19 booster dose	√			
Benefits and effectiveness of COVID-19 booster	√			
Safety of COVID-19 vaccines	√			
Indications and contraindications of COVID-19 vaccination		√		
Precautions for COVID-19 vaccination		√		
Testimony from older adults who received COVID-19 booster			√	
Daily SMS reminder^a﻿^				√

^a^SMS refers to short message service

### Manipulation checks

At the end of each intervention material, two simple questions about the content will be left to check manipulation. Only by answering both of the questions correctly can participants in the intervention arm get an additional symbolic reward (CNY 1, or USD 0.15).

### Outcomes

At Phase I, the primary outcome is college students’ willingness to persuade grandparents to receive COVID-19 vaccines, measured by the item “Would you like to encourage COVID-19 vaccination for your grandfather/grandmother?” (No, or Yes). In this item, college students were asked to report their intention to encourage COVID-19 vaccination for each of their grandparents. At Phase II, the primary outcome is grandparents’ uptake rate of COVID-19 booster dose, measured by the item “Have you (grandparents) received a COVID-19 booster dose?” (No, or Yes). Secondary outcomes include grandparents’ scores of attitude and intention to get a COVID-19 booster dose.

### Statistical analysis

All analysis will be performed using R (V.3.6.1, Foundation for Statistical Computing, Vienna, Austria). All effects will be estimated with 95% CI and *P* values. Statistical significance will be taken as two-sided *P* values < 0.05.

According to the types of the variables, descriptive statistical analysis will be carried out for all variables and outcomes, including count, frequency, ratio, mean, standard deviation, and so on. To test the reliability of all the Likert’s scale, Cronbach’s α test will be used.

At Phase I, the primary outcome is college students’ willingness to persuade their grandparents to receive COVID-19 vaccine. Considering that older adults will be nested in families, the condition that all participants are independent, as required for general logistic regression, does not hold. Thus, the multilevel logistic regression model will be necessary. Assuming that each college student has a different intercept, we will apply random intercept, fixed slop models to investigate factors associated with college students’ willingness. The fixed effects will be reported as adjusted odds ratio (AOR) while random effects will be reported by variance, intraclass correlation (ICC). The Akaike’s information criterion (AIC) will be used to determine the goodness of fit.

At Phase II, Chi-squared test will be used for between-group comparison of grandparents’ uptake of COVID-19 booster dose. Incidence rate ratio (IRR) and 95% CIs will be calculated with Poisson regression, adjusted for grandparents’ sex, age, type of residence, educational background, cohabitation history, living conditions, outdoors activities and chronic diseases. Subgroup analyses will be conducted according to grandparents’ sex, age, type of residence, educational background, cohabitation history and chronic diseases. We will use ANCOVA to analyze grandparents’ score of attitude towards COVID-19 booster dose and intention to get a COVID-19 booster dose. Outcomes will be assessed using both intention-to-treat (ITT) and per-protocol (PP) sets. The ITT analysis will calculate outcomes for all enrolled grandparents. The PP analysis will only include grandparents of grandchildren who successfully completed the questions embedded within the health education materials and completed a follow-up survey. To account for loss-to-follow-up, we will use multiple imputation by chained equations to impute missing values.

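### Phase II randomises students but names tests that treat their grandparents as independent, which understates the variance if outcomes within a family are positively correlated

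*Protocol article*

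**What the plan says.** Allocation is by student. Under Randomized controlled trial: "Eligible participants will be assigned to the intervention or control arm at a 1:1 ratio chronologically", and "College students with the order of enrollment corresponding to the smaller half of random numbers will be allocated to the intervention arm". The education package and the reminders also go to students.

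The outcome belongs to grandparents. Under Outcomes, for Phase II, "the primary outcome is grandparents’ uptake rate of COVID-19 booster dose", and under Statistical analysis, "The ITT analysis will calculate outcomes for all enrolled grandparents". The inclusion criteria ask for at least one eligible grandparent, so a student may contribute several. All of them fall in that student's arm.

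For Phase I, Statistical analysis states: "Considering that older adults will be nested in families, the condition that all participants are independent, as required for general logistic regression, does not hold". It then calls for a multilevel logistic model with a random intercept per student.

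The next paragraph, on Phase II, reads: "Chi-squared test will be used for between-group comparison of grandparents’ uptake of COVID-19 booster dose". It continues: "Incidence rate ratio (IRR) and 95% CIs will be calculated with Poisson regression", adjusted for characteristics of the grandparent only. Attitude and intention scores go to ANCOVA. None of these carries a random effect, a working correlation or a variance clustered on student.

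Under Sample size, 162 older adults per group are required (2.5% against four times that rate, 80% power, two-sided 5%), to be reached through at least 101 students. The text does not say whether 101 is per arm or in total.

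**The concern.** Phase II is in effect a cluster-randomised trial with the student's family as the cluster. Because the arm is constant within a cluster, the comparison of arms carries the full design effect. Grandparents of one student share one persuader and one person who reports their status, so positive correlation of their outcomes is likely. The protocol accepts that argument for Phase I and then drops it in the phase where it bears on the treatment comparison.

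At stake are the level of the primary test, the width of the intervals, the subgroup results and both secondary outcomes. The stated power is affected too, since the sample size rests on the same assumption of independence.

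**Working it through.** **1. Reproduce the sample size.** Inputs from Sample size: p1 = 0.025, p2 = 0.10, k = 1, z = 1.960 and 0.842. The mean rate is 0.0625.

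N = [1.960 × √(2 × 0.0625 × 0.9375) + 0.842 × √(0.025 × 0.975 + 0.10 × 0.90)]² / 0.075² = [0.671 + 0.285]² / 0.005625 ≈ 162.3

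This is 163 rounded up, and power at 162 is 79.9%. The stated 162 is therefore the figure for independent observations, with a design effect of 1.

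**2. Grandparents per student (m).** 162/101 = 1.60 if 101 is per arm; 324/101 = 3.21 if it is the total. Neither reading gives one grandparent per student.

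**3. Design effect, level and power.** The protocol gives no intraclass correlation (ICC), so 0.1 to 0.7 is assumed.

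- Design effect: DE = 1 + (m − 1) × ICC. The naive standard error is too small by a factor √DE.
- True level of the uncorrected test: 2 × [1 − Φ(1.96/√DE)].
- Power of a cluster-adjusted test: the formula of step 1 at an effective size of 162/DE.
- Grandparents per arm needed: 162 × DE.

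| m | ICC | DE | True level | Power at 162 | Needed per arm |
|---|---|---|---|---|---|
| 1.60 | 0.1 | 1.06 | 5.7% | 78% | 172 |
| 1.60 | 0.3 | 1.18 | 7.1% | 73% | 192 |
| 1.60 | 0.5 | 1.30 | 8.6% | 69% | 211 |
| 1.60 | 0.7 | 1.42 | 10.0% | 65% | 231 |
| 3.21 | 0.1 | 1.22 | 7.6% | 72% | 198 |
| 3.21 | 0.3 | 1.66 | 12.9% | 58% | 270 |
| 3.21 | 0.5 | 2.10 | 17.7% | 49% | 341 |
| 3.21 | 0.7 | 2.55 | 21.9% | 42% | 413 |

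The standard error is understated by a factor of 1.03 to 1.19 at m = 1.60 and 1.10 to 1.60 at m = 3.21.

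**4. Simulation.** Beta-binomial data, 20,000 replicates per setting, 162 grandparents per arm, family sizes as equal as possible, the same uptake in both arms. The Poisson test is the model-based Wald test with arm only. Entries are rejection rates in % for ICC 0.1 / 0.3 / 0.5 / 0.7.

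| Setting | Chi-squared, uncorrected | Chi-squared, continuity-corrected | Poisson, model-based |
|---|---|---|---|
| m = 1.60, uptake 2.5% | 4.9 / 7.0 / 8.9 / 10.4 | 2.0 / 3.1 / 4.3 / 5.1 | 1.2 / 2.0 / 2.7 / 3.0 |
| m = 1.60, uptake 10% | 6.1 / 7.5 / 9.9 / 11.4 | 3.8 / 4.9 / 6.8 / 8.1 | 4.4 / 5.4 / 7.4 / 8.8 |
| m about 3.2, uptake 2.5% | 7.0 / 12.4 / 18.1 / 23.4 | 2.9 / 6.5 / 10.3 / 13.9 | 2.0 / 4.0 / 5.5 / 5.9 |
| m about 3.2, uptake 10% | 7.6 / 13.1 / 18.4 / 23.4 | 5.1 / 9.6 / 14.3 / 19.0 | 5.6 / 10.2 / 15.2 / 19.8 |

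A test with variance clustered on student rejected in 4.9% to 5.4% at 10% uptake and in 5.1% or less at 2.5%.

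**5. Unequal family sizes.** These raise the design effect. With an assumed mix of 1 to 4 grandparents (mean 1.61), 5% to 10% uptake and ICC 0.3 to 0.7, the uncorrected test rejected in 8.3% to 14.8% (4,000 runs per setting). The protocol gives no size distribution, so this is only an illustration.

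**The case against.** One defence is that an article condenses the full plan and that clustering may be handled elsewhere. It does not stand: the article spells out the clustered model for Phase I and then names independence-based methods for Phase II. That is a stated choice, not an omitted detail.

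The objections to size and certainty have more force.

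- A reader might infer that the 5% level is certainly broken and every interval certainly too narrow. The documents do not support that. They give no ICC and do not say whether the chi-squared test is continuity-corrected. At the protocol's own 2.5% rate with 1.6 per student, the corrected test rejects in about 2% to 5% and the model-based Poisson test in about 1% to 3%. Even the uncorrected test is at 4.9% when the ICC is 0.1.
- A reader might count Poisson regression on a yes/no outcome as a further source of optimism. It works the other way: its model-based standard error is too wide by 1/√(1 − p), about 1% at 2.5% uptake and 5% at 10%, and partly offsets the clustering.
- A low ICC cannot be excluded. A student's grandparents may be couples on different sides of the family.
- The figures at 3.2 per student need 101 to be the total and most students to have three or four grandparents who are living, aged at least 60, fully primed and not boosted. That reading is possible but strained, and it should not carry the headline.

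None of this makes the named methods right. An error that is sometimes cancelled by few events or a conservative variance is not controlled.

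**Conclusion.** The point holds in conditional form, and the Phase II analysis is wrong as written: it contradicts the protocol's own statement on nesting. Given positive correlation within a student's family, the named methods understate the variance.

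For the uncorrected chi-squared test with ICC 0.1 to 0.7, the level is about 5.7% to 10% at 1.6 grandparents per student, somewhat more with unequal families. If 101 is the total number of students it is about 7.6% to 22%. For the corrected test or the model-based Poisson interval the inflation is smaller. It may be absent at 2.5% uptake with 1.6 per student, but it appears at higher uptake, higher ICC or larger families.

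The direction rests on positive correlation, which is likely. The size rests on an assumed ICC and on what 101 means. The loss of stated power does not depend on which naive test is chosen: a valid test at 162 per group has less than 80% power at any positive ICC.

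**What to change.** In Statistical analysis, make the Phase II primary comparison a student-clustered one: modified Poisson regression on grandparents with robust standard errors clustered on student, or GEE with the student as cluster. Either also corrects the Poisson variance for a yes/no outcome. Replace the plain chi-squared test by a cluster-adjusted version, or label it descriptive. Apply the same clustering to the ANCOVA of attitude and intention and to the subgroup models.

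In Sample size, say whether 101 students is per arm or in total, state the assumed ICC and the grandparents per student, and restate the power of 162 per group with the design effect. If 80% is to be kept, the target rises to about 172 to 231 per arm at 1.6 per student, or 198 to 413 at 3.2.

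The change of analysis needs no new data, since each student answers for his or her own grandparents; it takes revised wording and a few lines of R. The cost is somewhat wider intervals and either a less favourable stated power or more students to recruit.

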### Ethics and dissemination

The study has been approved by the ethical review committees at School of Public Health (Shenzhen), Sun Yat-sen University. Participants’ identifiable information (name, ID card number, address, etc.) will not be collected. Meanwhile, for ethical reasons, all participants in the control arm will receive the same intervention materials as the intervention arm at the end of the study.

## Discussion

As college students play an increasingly important role in family decision-making, grandchild-mediated vaccine promotion strategy at the family level shows potential value. This study protocol focuses on this interesting issue and is the first to describe an approach combing a cross-sectional and a randomized controlled trial to discuss the effect of college students’ persuasion on COVID-19 vaccination uptake in older adults. First, a cross-sectional study will be applied to help us understand the willingness of college students’ persuasion and related factors, which indicate the preliminary feasibility of a latent and cost-effective new strategy to promote vaccination in older adults. The reason behind those college students who are reluctant to persuade may inform future interventions aimed at improving their willingness to persuade. Meanwhile, cross-sectional study in our protocol plays a dual role in providing theoretical assumptions and participant recruitment for randomized controlled trial, which is more efficient than two separate studies otherwise. Second, combined with traditional socio-demographics, HBM and TPB theoretical models are applied to comprehensively explain the behavior of college students’ persuasion to their grandparents on COVID-19 vaccination, which may shed light on innovative and potentially feasible measures to improve vaccine uptake in older adults. Third, surveying older adults through college students not only simplifies personnel recruitment, but also avoids problems in the research process caused by dialect barriers and transportation inconveniences. Lastly, we will conduct a randomized controlled trial to determine the effect of college students’ persuasion on COVID-19 vaccination in older adults. Of note, China has more than 3000 colleges and more than 55 million college students [34]. With foreseeable potential cost effectiveness, this intervention will contribute to promote the formulation of working guidelines for the scale-up of COVID-19 vaccination among older adults in China and beyond.

This study faces potential challenges. First, the information of older adults reported by college students may not reflect their grandparents’ real situation. To mitigate this issue, participants who give the answer “unclear” to questions about older adults at Phase I will be excluded at Phase II. At Phase II participants will be asked to inquire their grandparents before completing the questionnaires. Second, the interval between Phase I and Phase II cannot be ignored. Grandparents’ COVID-19 vaccination status may change during this period. So we will double-check the actual vaccination status of grandparents to confirm participants’ eligibility. Third, the whole study procedure is based online, and the validity of the results will be affected [35, 36]. In our design, we target college students, who are highly educated and frequently accessed the Internet, to reduce the selection bias of the online survey [37]. Monetary incentives will be provided to reduce the risk of loss to follow-up [35]. The process of intervention will be followed by SMS reminders and quizzes to engage participants and improve the effect of web-based intervention. At the same time, through the logical verification of the three questionnaires and additional information about participants outside the questionnaire (IP address, response time, etc.), latent survey fraud can be partly prevented [38].

In summary, the knowledge gained from this study may be used to develop a grandchild-mediated strategy to promote COVID-19 vaccination in older adults, which may enrich vaccine promotion strategies for older adults in China and beyond.

## Data Availability

The data collected in this study will not be publicly available. However, the corresponding author can be contacted for de-identified data on reasonable request.

## Abbreviations

COVID-19: Coronavirus disease 2019
KAP: Knowledge, attitude and practice
HBM: Health Belief Model
TPB: Theory of Planned Behavior
SMS: Short message service
